#### Patients’ satisfaction with SMS reminders

First, we will analyze the psychometric quality of the questionnaire items. Cronbach’s alpha, McDonalds’s hierarchical omega, as well as Mokken scale analysis [95] will be used to find out if all items have sufficient quality to be included in the final scale. In case of significant deficiencies, item(s) will be excluded. Second, using the final scale, we will analyze the impact of patient satisfaction level on the change of adherence and systolic blood pressure values via multivariate linear regression, controlling for impact of sex, age, education, etc. This way we strive to find out if the overall satisfaction level of patients is a significant predictor variable for the change in ARs and/or systolic blood pressure values.

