## Methods

### Trial objectives

The primary objective of the SPPA trial is to assess if daily SMS reminders of antihypertensive medication intake provided by pharmacists in addition to the sPhC increase the proportion of adherent older hypertensive ambulatory patients.

Secondary objectives include: (1) comparing the change of self-reported adherence using the eight-item Morisky Medication Adherence Scale (MMAS-8); (2) comparing ARs measured via pill count between trial groups; (3) comparing the change in systolic blood pressure; (4) investigating the effect of SMS reminders on improving patients’ adherence and systolic blood pressure control (treatment effects) across subgroups; and (5) collecting and reporting patients’ satisfaction with daily SMS reminders.

We will report up-to-date ARs of older hypertensive patients in Slovakia and assess the impact of sociodemographic characteristics on patients’ adherence to antihypertensive medicines. Furthermore, we will evaluate the MMAS-8 questionnaire in our trial population. Additionally, we will carry out a simple cost-effectiveness analysis from the payers’ perspective.

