### Outcome measures

#### Primary outcome measure

Our primary outcome is the proportion of adherent patients in the intervention group after three months of receiving SMS reminders of medication intake. For these purposes, we will assess patients’ adherence via combined adherence endpoint consisting of self-reported medication adherence measured via MMAS-8 and pill count rate (%).

The eight-item MMAS questionnaire, on which the MMAS-8 is based, evaluated hypertensive patients. It showed good reliability (α = 0.83) as well as sensitivity (93%) and specificity (53%) in the identification of lower versus higher adherence to antihypertensive medication. Additionally, the association between MMAS-8 and blood pressure control was proved statistically significant (*p* < 0.05) [19]. Each question aims at assessing a specific medication-taking behavior, either intentional or unintentional. The first seven questions have dichotomous answers (yes/no), whereas the last question offers a five-point Likert response. The range of the scores is from 0 to 8 with 0 being low adherence and 8 indicating full medication adherence [19, 74].

Pill count is a simple objective indirect measurement of patients’ adherence to medication intake [75]. AR will be calculated using the following equation:$$ \mathrm{A}\mathrm{R}\left(\%\right)=\left(\frac{\mathrm{No}.\mathrm{of}\;\mathrm{pills}\;\mathrm{actually}\;\mathrm{taken}}{\mathrm{No}.\mathrm{of}\;\mathrm{pills}\;\mathrm{that}\;\mathrm{should}\;\mathrm{have}\;\mathrm{been}\;\mathrm{taken}}\right)\times 100 $$

No specific guidelines exist on how to assess medication adherence [76]; therefore, we based our categorization of a patient as being “adherent” or “non-adherent” on the previous literature and expert opinions. Our study team agreed that a patient at the end of the trial will be considered as either “adherent,” having MMAS-8 ≥ 6 [19] and pill count rate ≥ 80% [77], or “non-adherent” if one or both of the previous conditions are not met. Table 3 contains details on our primary outcome measure.

**Table 3 Tab3:** Primary outcome Combined adherence endpoint

Level	
Domain	Combined medication adherence
Specific measurement variable	Adherence status (dichotomous) adherent: MMAS-8 score ≥6 and pill count rate ≥80% non-adherent: MMAS-8 score <6 and/or pill count rate <80%
Analysis Metric	Final value (Visit 2)
Method of aggregation	Proportion of adherent patients (%)

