#### Secondary outcome measures

Table 4 summarizes the details of our secondary outcome measures. We will also evaluate the clinical outcome – blood pressure, which is highly emphasized to provide information on the relationship between medication adherence and blood pressure control [33]. Considering our trial population, consisting of older patients, we have decided to evaluate only systolic blood pressure, not diastolic blood pressure, in our secondary clinical outcome. First, diastolic blood pressure is known to paradoxically decrease with increasing age in patients aged above 55 years [78]. Second, diastolic blood pressure has shown to be less predictive in regard to decrease in cardiovascular morbidity and mortality [79]. We prepared a detailed guidance for blood pressure measurement (SPPA Scheme for Blood Pressure Measurement is available within Additional file 3) based on the current international recommendations for blood pressure measurement [4, 80]. Trial pharmacists will be re-trained on all steps and will comply with the SPPA Scheme for Blood Pressure Measurement during the whole trial, which will ensure that all blood pressure measurements will be performed uniformly.

**Table 4 Tab4:** Secondary outcomes

Secondary outcome	Change in medians of MMAS-8	Mean adherence rate after 3 months	Mean change in systolic blood pressure
Domain	Self-reported medication adherence (MMAS-8 questionnaire)	Medication adherence (pill count)	Blood pressure (manometer)
Specific measurement variable	MMAS-8 (categorical, ordinal)	Adherence rate in % (numerical, continuous)	Systolic blood pressure in mmHg (numerical, continuous)
Analysis Metric	Change from baseline (Visit 1)	Final value (Visit 2)	Change from baseline (Visit 1)
Method of aggregation	Median	Mean	Mean
Time point of measurement	Visit 1 Visit 2	Visit 2	Visit 1 Visit 2

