#### Mean adherence rates after three months calculated via pill count

The mean difference in adherence reported as AR (%) measured at Visit 2 between the intervention and the control groups will be calculated. The effect size and the corresponding 95% CI will be reported. We will use a two-tailed t-test to compare the difference between these independent means as well as their robust versions that are recommended when conditions for these tests are violated while preserving high statistical power.

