#### Subgroup analysis

We will conduct a subgroup analysis of the SMS reminders’ effect on improving adherence and systolic blood pressure (treatment effects) across subgroups based on: sex, baseline systolic blood pressure, number of years with hypertension, education level, number of daily antihypertensive medications, frequency of antihypertensive medication intake, and baseline self-reported AR according to MMAS-8. We will use the QUINT (Qualitative INteraction Trees) package in R software for a qualitative subgroup analysis to detect different direction of impact for various subgroups [96].

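### The satisfaction regression names change in AR as an outcome, but AR is a pill-count percentage recorded only at Visit 2, so that change cannot be computed

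*Protocol article*

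**What the plan says.** All references are to the protocol article.

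- **Patients' satisfaction with SMS reminders (Statistical analysis).** The method sentence plans to study the "impact of patient satisfaction level on the change of adherence and systolic blood pressure values via multivariate linear regression", with adjustment for sex, age, education and similar factors. The next sentence gives the aim: to learn whether the overall "satisfaction level of patients is a significant predictor variable for the change in ARs and/or systolic blood pressure values".
- **Primary outcome measure.** "AR will be calculated using the following equation"; the equation is pills taken over pills that should have been taken, times 100. This is the only formula for AR in the document.
- **Trial objectives.** The second secondary objective uses the term in the same sense: "comparing ARs measured via pill count between trial groups".
- **Secondary outcome measures, Table 4.** The pill-count outcome is "Adherence rate in % (numerical, continuous" with the metric "Final value (Visit 2". MMAS-8 and systolic pressure both have change from baseline as their metric.
- **Mean adherence rates after three months calculated via pill count.** The comparison is "The mean difference in adherence reported as AR (%) measured at Visit 2".
- **Subgroup analysis.** One listed factor is "baseline self-reported AR according to MMAS-8".

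**The concern.** The aim sentence names an outcome that the data schedule cannot supply. A change needs two measurements, and AR as defined has one. Whoever programmes this analysis must replace the stated outcome with something else, and the text does not say what. The candidates are different endpoints: change in MMAS-8 is a self-report measured twice, and Visit 2 pill count is a count measured once. If the choice is left open until the data are available, it can be made with the results in view.

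The loose use of AR in the Subgroup analysis section adds to the ambiguity. If AR can also mean an MMAS-8 result, a change in AR could be read as a change in MMAS-8, although the formula and Table 4 say otherwise.

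At stake is one exploratory result: whether satisfaction is related to adherence.

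**Working it through.** No formula or sample size bears on this, and the plan states no figure to reproduce. The check is to set each possible outcome against the visits at which it is collected.

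**Step 1. When is each quantity recorded?** (Table 2 and Table 4)

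| Quantity | Visit 1 | Visit 2 | Metric in Table 4 | Can a change be formed? |
|---|---|---|---|---|
| Pill-count AR | no | yes (Part A) | final value | no |
| MMAS-8 | yes (Part C) | yes (Part C) | change from baseline | yes |
| Systolic pressure | yes (Part B) | yes (Part B) | change from baseline | yes |

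None of the four Visit 1 forms (Parts A to D) holds a pill count. This is by design. The rationale after the exclusion criteria explains that counting is meant to start from the package collected at enrolment, with the first pill usually taken the next day. There is no earlier period for which a count could exist.

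**Step 2. What does AR mean in each place?** It is the pill-count percentage in the Primary outcome measure section, the second secondary objective, Table 4 and the pill-count analysis section. It is a baseline MMAS-8 result in the Subgroup analysis section. In the Background it is the share of a population that is adherent. Only the first sense has a formula.

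**Step 3. What follows for the satisfaction regression?**

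- Change in pill-count AR: one time point, so it is available for no participant.
- Change in MMAS-8: two time points, so it can be computed. Its Visit 2 part is self-reported, as satisfaction is. The Participant timeline section lists both questionnaires, with the pill count, in the telephone substitute for the follow-up visit, which suggests that they are normally collected at the same contact.
- Change in systolic pressure: two time points, measured by the trial pharmacist, so it can be computed and is not a self-report.

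**Step 4. Does it matter whether the outcome is a change or a final value?** For a variable measured twice, once its baseline is in the model it does not. Write Y1 and Y2 for the baseline and follow-up values and S for satisfaction. The model Y2 − Y1 = a + bS + cY1 rearranges to Y2 = a + bS + (c + 1)Y1, with the same coefficient b for satisfaction. Adding the baseline therefore settles that choice for MMAS-8 and systolic pressure. It does not help pill count, which has no Y1; there the Visit 2 value has to stand as a final value, with baseline MMAS-8 as the available measure of prior adherence.

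**The case against.** The strongest reply is that a workable reading already exists. The method sentence speaks of a change of adherence, not of AR, and Table 4 defines exactly one adherence change, that in MMAS-8. AR is also expanded in the abbreviation list simply as adherence rate, and the text often adds a qualifier when a particular measure is meant. On this view the aim sentence is a slip that a careful analyst would resolve correctly. This stands in part: it makes the problem one of wording. It does not remove it, because the two adjacent sentences do not name the same measurable outcome.

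Several stronger conclusions might be inferred, and the documents do not support them.

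- *The whole regression fails.* It does not. Systolic pressure is named in the same sentence and can be analysed.
- *AR has competing definitions.* It has one formula. The Subgroup analysis wording is a loose label and does not define AR a second time.
- *Using MMAS-8 would produce a spurious association through response style.* The documents give no correlation from which to judge this. A stable tendency to answer favourably raises MMAS-8 at both visits and largely cancels in the change, ceiling effects aside. Shared self-report calls for caution in interpretation; it is not an error in the plan.
- *Later decisions rest on this regression.* The Sample size calculation section makes a larger study depend on effectiveness and on satisfaction being high, and the Discussion uses patient-reported outcomes to adjust the intervention. Neither refers to the regression.
- *Pill count should be the only adherence outcome here.* The Discussion itself concedes that pill count used alone is often not valid, so demoting MMAS-8 would be a debatable preference.

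**Conclusion.** The point holds in a limited form. As AR is defined and collected, a change in AR cannot be computed for any participant, and the satisfaction section should not name it as an outcome. This rests on the formula, Table 2 and Table 4, which agree with one another, and needs no numerical assumption.

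The size is minor. One of the two outcomes of an exploratory secondary regression is affected. The related objective promises only to collect and report satisfaction, and the regression does not appear in Table 4. The primary comparison and the sample size are untouched.

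Two inferences are used. The models are taken to concern the intervention arm, because the questionnaire asks about satisfaction with the reminders. Satisfaction and Visit 2 MMAS-8 are taken to be collected at the same contact, from the telephone procedure.

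**What to change.** In the satisfaction section:

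1. Replace change in AR with two named adherence outcomes, both reported: change in MMAS-8 as in Table 4, and Visit 2 pill-count AR as a final value. Keep change in systolic pressure.
2. State that the models are fitted in the intervention arm.
3. Add baseline MMAS-8 to both adherence models and baseline systolic pressure to the blood pressure model, alongside the covariates already listed.
4. Describe the result as an association, and note that satisfaction and Visit 2 MMAS-8 are both self-reported.

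Elsewhere in the plan, reserve AR for the pill-count percentage and call the subgroup factor the baseline MMAS-8 score.

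The cost is wording only. Every variable is already planned for collection, and no visit, form or sample size changes. The edit should be made before database lock, so that the adherence outcomes are fixed before the data are seen.

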#### Subgroup analysis

We will conduct a subgroup analysis of the SMS reminders’ effect on improving adherence and systolic blood pressure (treatment effects) across subgroups based on: sex, baseline systolic blood pressure, number of years with hypertension, education level, number of daily antihypertensive medications, frequency of antihypertensive medication intake, and baseline self-reported AR according to MMAS-8. We will use the QUINT (Qualitative INteraction Trees) package in R software for a qualitative subgroup analysis to detect different direction of impact for various subgroups [96].

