### Sample size calculation

In the recent multinational survey, adherence prevalence in European countries was in the range of 30–76% [25]. Given the results of the latest national study reporting even lower ARs [28], we assume 30% adherence prevalence in the control group. According to a meta-analysis of randomized clinical trials, SMS reminders had the potential to double the odds ratio (OR) of medication adherence (OR = 2.11; 95% confidence interval [CI] = 1.52–2.93; *p* < 0.001) in cardiovascular patients. The weighted mean effect size was d = 0.41 (95% CI = 0.23–0.59). After adjusting for publication bias, the odds of being adherent in the group receiving SMS reminders was 68% higher than in the control group (OR = 1.68; 95% CI = 1.18–2.39) [50]. Results of the StAR trial carried out in a hypertensive population support these results, reporting an OR of 1.86 (95% CI = 1.20–2.16; *p* = 0.002) for improved adherence in patients receiving SMS reminders [84]. Therefore, we hypothesize that SMS reminders of antihypertensive medication intake can improve the proportion of adherent older patients in Slovakia from 30% to 49% given an effect size of w = 0.2 (equivalent to d = 0.4). Using a χ2 test of independence, a total of 264 patients are needed to reject the null hypothesis that the adherence proportions in both groups are equal with a power of 0.9 and alpha of 0.05. Considering approximately a 10% attrition rate, we plan to enroll 300 patients (150 in each group). Previous studies reported attrition rates of 3.2% [71], 12.8% [84], and 19.0% [70]; while the major reason for loss of participants was unwillingness or impossibility to attend the follow-up visit(s). Slovak chronic hypertensive patients are already used to regular visits of pharmacies in approximately three-month cycles. Since our trial is embedded within usual pharmaceutical care provision, we expect a lower drop-out, as in the EmPhAsIS study [85].

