#### Other outcomes analyses

We will assess internal consistency of the MMAS-8 scale in our trial population by Cronbach’s alpha coefficient and reliability of the summed score by McDonald’s hierarchical omega, which has been shown to be a superior measure to Cronbach’s alpha [97]. We will also provide the measures of sensitivity and specificity of MMAS-8 related to correct prediction of high blood pressure. Of interest is also the relationship between two measures of adherence (MMAS-8 and pill count), which will be analyzed using correlation coefficients (Pearson and Kendall tau). Additionally, regression techniques to analyze the impact of co-variables, such as: age, gender, education level, social status, place of residence, number of daily doses, co-medication, co-morbidities (concomitant diseases, smoking status), and pharmacy on patients’ adherence will be applied.

Since we are interested in providing relevant information for the decision-making process, we will conduct a simple cost-effectiveness analysis. Here, we will focus only on the differential costs that depend on the choice of alternative care (usual pharmaceutical care or SMS reminder).

Finally, we will collect, report, and perform a qualitative analysis of the refusal to participation in the trial and withdrawal from the trial rates.

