The main limitation of the SPPA trial is that our current sample size lacks statistical power to detect significant change in clinical outcome, the systolic blood pressure. Also, the SPPA trial is not designed to focus on other important clinical outcomes such as cardiovascular risk reduction, prevention of cardiovascular events, or overall cardiovascular mortality. Furthermore, we formulate the SMS content solely to remind patients of their medication intake, not to educate or motivate them in any specific way, as some previous studies have intended [70, 84, 103]. Thus, our investigated intervention addresses only unintentional non-adherence due to forgetfulness, not intentional non-adherence. We have opted for this intervention since the majority of Slovak patients report forgetting as the major cause of non-adherence [98]. Moreover, pharmacies are highly accessible in Slovakia and at least one antihypertensive drug within each class is fully reimbursed by the public health insurance. Access to antihypertensive medicines is therefore not an obstacle for patients’ adherence in Slovakia.

Additionally, we collect patients’ health and medication information as patient-reported outcomes. Since pharmacists in Slovakia do not have access to patients’ health or medication history, patients are their only source of this information also in everyday practice. Thus, on the one hand, our pragmatic trial design reflects everyday practice; on the other hand, it also presents a limitation relying on the memory and truthfulness of the patients.

Another limitation of the study is that pill count assessment used alone, as in our secondary analysis, is often not valid. Patients may tend to remove their pills before the visit to please the healthcare provider who performs the pill count. Nevertheless, we have decided to include this outcome in our secondary analysis based on the following rationale. First, pill count as a research method is not frequently used in Slovakia and we will not explicitly inform the participants that their pills will be counted. Hence, participants will not be alerted to this fact. Second, we assume that patients’ primarily want to please their physician, who prescribed them the medicines and not necessarily the pharmacist, viewed more as a trusted counselor, in front of whom there is no need to hide information on medication intake.

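### The only subgroup method named looks for reversals of effect, while secondary objective 4 covers any difference in treatment effect across subgroups

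*Protocol article*

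**What the plan says.** In the Protocol article, Trial objectives, the fourth secondary objective is "investigating the effect of SMS reminders on improving patients’ adherence and systolic blood pressure control (treatment effects) across subgroups". It is not limited to reversals of direction.

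The Subgroup analysis section repeats the aim: "We will conduct a subgroup analysis of the SMS reminders’ effect on improving adherence and systolic blood pressure (treatment effects) across subgroups based on". It lists seven factors: sex, baseline systolic pressure, years with hypertension, education, number of daily antihypertensive medications, frequency of intake, and baseline MMAS-8. It then names one method, "We will use the QUINT (Qualitative INteraction Trees) package in R software", and gives its purpose: "for a qualitative subgroup analysis to detect different direction of impact for various subgroups".

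Two other sections mention regression. Other outcomes analyses plans "regression techniques to analyze the impact of co-variables" on adherence. The section on patients' satisfaction uses satisfaction level to predict change in adherence and systolic pressure. Neither mentions a treatment-by-factor term.

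On mechanism, the Discussion says that "our investigated intervention addresses only unintentional non-adherence due to forgetfulness, not intentional non-adherence".

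**The concern.** The objective asks how the treatment effect varies across subgroups. The named method, by the article's own description, asks whether the effect changes sign. The second question is narrower.

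The protocol's rationale points to the kind of variation left out. A reminder that acts only on forgetting should do most for patients who forget and little for those who skip doses deliberately. The inclusion criteria set no upper limit on baseline adherence, so patients already at MMAS-8 of 6 or more can enrol, and they have little room to improve on that component. Both considerations suggest a large effect in some patients and a small one in others. The article gives no reason to expect reminders to reduce adherence in any listed subgroup, although it does not exclude this.

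At stake is how a secondary objective is read. A search for reversals that finds none leaves differences in size unexamined. Interaction models chosen after the data are seen would be post hoc.

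**Working it through.** **Step 1. Objective against method.** Objective 4: effect on adherence and systolic pressure across subgroups, with no restriction on the kind of difference. Subgroup analysis, first sentence: the same, for seven factors. Subgroup analysis, method: QUINT, for differences in direction. The two regression sections contain no treatment-by-factor term. No named analysis is aimed at same-direction differences.

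**Step 2. The plan's own figure.** Inputs from Sample size calculation: 30% versus 49%, w = 0.2, alpha 0.05, power 0.90, total 264. With 1 degree of freedom the noncentrality is 264 × 0.2² = 10.56, which gives power 0.901. The 264 is reproduced. No figure is stated for the subgroup analysis.

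**Step 3. A same-direction contrast that fits the planned effect.** Assume two subgroups of equal size, so 264 / 4 = 66 patients per arm per subgroup.

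*Scenario A:* 20% to 48% (+28 points) and 40% to 50% (+10 points).
- Averages: control (20 + 40)/2 = 30%, intervention (48 + 50)/2 = 49%, as planned.
- Odds ratios: (0.48/0.52)/(0.20/0.80) = 3.69 and (0.50/0.50)/(0.40/0.60) = 1.50.
- Difference in log odds ratios: 1.306 − 0.405 = 0.901.
- SE = √Σ 1/[66p(1−p)] = √(0.0947 + 0.0607 + 0.0631 + 0.0606) = 0.528.
- z = 0.901/0.528 = 1.705. Power = Φ(1.705 − 1.96) = 0.40.
- Ratio of odds ratios 3.69/1.50 = 2.46. Expected 95% CI exp(0.901 ± 1.96 × 0.528), about 0.87 to 6.9.

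*Scenario B:* control 30% in both subgroups; 58% (+28) and 40% (+10) with reminders.
- Risk-difference scale: SE = √[(0.21 + 0.2436 + 0.21 + 0.24)/66] = 0.117; z = 0.18/0.117 = 1.538; power 0.34 (0.37 at 75 per cell, all 300 analysed).
- Log-odds scale: difference 1.170 − 0.442 = 0.728; SE = √[(1/0.21 + 1/0.2436 + 1/0.21 + 1/0.24)/66] = 0.519; z = 1.402; power 0.29.

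*Scenario C:* control 30% in both; 64% (+34) and 34% (+4).
- Risk-difference scale: SE = √[(0.21 + 0.2304 + 0.21 + 0.2244)/66] = 0.115; z = 2.606; power 0.74 (0.79 at 75 per cell).

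B and C also average to 49% with reminders. None of the three contains a true reversal, so a search for opposite directions has no true target in any of them.

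**Step 4. Systolic pressure.** With the article's SD of 20 mmHg and no gain from baseline adjustment, the interaction SE is 20 × √(4/66) = 4.92 mmHg, a 95% CI half-width of 1.96 × 4.92 = 9.65 mmHg.

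**Step 5. Multiplicity.** Seven factors × two outcomes = 14 interaction terms. If no interaction existed, 14 × 0.05 = 0.7 nominally significant results would be expected.

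**The case against.** The strongest reply is that the first sentence of the Subgroup analysis section promises a general analysis, and QUINT may serve only its qualitative part. This is a condensed article. Interaction terms and exploratory labels often sit in an analysis plan, and that plan is not shown. This stands in part: ordinary subgroup estimates are not excluded. But the article does more than stay silent. It names a method and gives it a purpose narrower than the objective.

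A second reply is that reversals are worth looking for, since they would bear most directly on who should be offered the service, and that expecting same-direction effects is a judgement. Both points are fair. They support keeping QUINT, not using it as the only named method.

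A third reply is that the alternative is weak. It would miss the +28 versus +10 contrast 60% of the time or more, over as many as 14 terms. This stands. It is a reason to rely on intervals and an exploratory label.

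A reader might also infer more than the article supports:
- That the trial cannot address objective 4. The data are collected and other estimates are not ruled out; only the named method falls short.
- That a same-direction difference would be reported as no subgroup difference. No section sets such a rule.
- That the larger study would be mistargeted. The article ties later research to effectiveness, satisfaction and systolic pressure results, and never says subgroup findings will select patients.
- That QUINT yields no usable estimates. The article does not describe its output.

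**Conclusion.** The point holds as a mismatch between a stated objective and the one method named for it. QUINT, as the article describes it, is not aimed at treatment effects that share a direction and differ in size, and the forgetfulness rationale makes that the more plausible pattern. The mismatch rests on the text alone.

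The figures show what an interaction analysis could and could not deliver. For +28 versus +10 points at 66 per cell, power is 29% to 40%; only an extreme contrast such as +34 versus +4 reaches about 74% on the risk-difference scale. They assume two equal subgroups, invented subgroup rates that average to the planned 30% and 49%, a two-sided 5% test and no multiplicity adjustment. Unequal subgroups of the same total would give less power.

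This is worth correcting before analysis, but it concerns an exploratory secondary objective. The primary comparison and its sample size are untouched.

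**What to change.** Rewrite the method sentence of the Subgroup analysis section so that:

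1. For each of the seven factors, one model with a treatment-by-factor term is pre-specified: logistic for the combined adherence endpoint (taking that as the adherence outcome meant), and linear with baseline adjustment for systolic pressure.
2. Baseline systolic pressure, years with hypertension and baseline MMAS-8 enter as continuous variables, without cut-points.
3. Each interaction estimate is reported with its 95% confidence interval. The whole set is labelled exploratory, with low power and no multiplicity control.
4. QUINT is kept as a supplementary search for reversed effects, with a statement that finding no partition is not evidence that effects are equal across subgroups.

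The cost is one paragraph of text and up to 14 models on data already collected. The drawback is more exploratory estimates to report, most with wide intervals. No change to design, sample size or primary analysis is needed. If an existing analysis plan already contains such models, a sentence pointing to it is enough.
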